### Statistical analysis

After performing data cleaning and imputation, exploratory analysis and categorization or transformation of variables the following analyses will be performed:

- Comparison of the variables of interest and the stratification and potentially confounding variables in the treated and non treated groups at the start of the study. We will determine if, despite using randomized assignment, the two groups are homogenous.

- A first raw analysis will be performed to calculate the following parameters and their confidence intervals: ARR (absolute risk reduction), RRR (relative risk reduction) and NNT (number necessary to treat). A stratified analysis will also be performed adjusting for each independent variable. If there are differences between the raw RR and the adjusted RR, the homogeneity between the categories will be determined to establish if the variable is effect modifying or confounding. The incidence of the variables in each group will be described and compared (comparison of proportions by the chi-squared test).

- A survival (fall-free period) analysis will be performed in both study groups (Kaplan-Meier and Log Rank test). Then the effect of treatment on the risk of falls will be determined by constructing a Cox proportional hazards model.

- The effect of treatment on calcium and vitamin D levels will be estimated adjusted for changes in treatment compliance (generalized linear models for repeated measures).

Data will be analyzed on an intention to treat basis including all randomized patients in the efficacy and safety analyses according to their randomized treatment group regardless of the treatment received. A per protocol analysis will also be performed for the primary variables. This will exclude patients who did not meet any of the selection criteria and did not comply with treatment.

For ethical reasons an intermediate analysis will be performed to decide if the study should be discontinued prematurely because of frequent adverse effects occur or an obvious improvement in the test group.

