### Definitions of the primary variables and measuring methods

The primary variable will be the incidence of spontaneous falls according to the FICSIT (Frailty and Injury: Cooperative Study of Intervention Techniques) definition: "Unintentionally coming to rest on the ground, floor, or other lower level. Coming to rest against furniture or a wall was not counted as a fall." Information on the circumstances of the fall (apparent cause, activity performed, time and place and need of help) will be obtained by an interview.

The following are the secondary variables:

- Consequence of falls (bone fractures at any location, need for healthcare, need for hospitalization, bed-ridden).

- Change in calcidiol [25(OH)D3] plasma levels (determined by RIA at baseline and at 6 and 18 months). Vitamin D deficiency is defined as a calcidiol plasma level lower than 10 ng/ml.

- Levels of transaminases, parathyroid hormone (PTH), calcium, phosphorous and serum creatinine, determined by tests on venous blood samples obtained in a fasted state. Calcium/creatinine index, determined by analysis of second morning urine.

- Change in bone mass (bone density or mineral content) obtained by densitometry (risk of fracture). Osteoporosis will be diagnosed based on a densitometry T-score of less than 2.5 in the vertebral column, according to WHO criteria.

- Change in muscle strength in the dominant hand. Determined by dyanometry (with a mean of 3 attempts to obtain a muscle strength measurement).

- Changes in musculoskeletal function, determined by the timed up and go test (the elderly person gets up from a chair with arms, walks three meters, turns round, walks back and sits down again). Taking more than 20 seconds indicates a high risk for falls.

- Stratification and potentially confounding variables; gender, age and other demographic data (social class, education level, marital status).

- Risk factors for falls: taking pre-disposing medication, health problems, toxic habits, physical exercise, living arrangements, sight or hearing difficulties, functional status (Katz index).

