## Discussion

If calcium and vitamin D supplementation is effective in the prevention of falls and fractures in the elderly population, a recommendation may be issued with the aim of preventing some of the consequences of falls that affect quality of life and the ensuing personal, health and social costs.

Using a randomization procedure will reduce selection bias as the investigator does not assign the treatment and any factor affecting participation will be equally divided between the two groups. Confounding is also reduced because randomization tends to share the determining factors that may affect the final result equally among the groups.

However, bias in the collection of information could occur in the study, such as patient evolution, determined by the aging process throughout the two study years, also the regression toward the mean or tendency of the continuous variables to approach the mean value in successive measurements. In our case this is applicable to the number of falls by the elderly people or the analytical test results. Furthermore, the participants, who are aware of the study objectives, could contribute to what is termed "hypothesis guessing" and try to downplay the importance of falls without consequences. There will also be a possible risk of differential loss to follow up between the groups being compared, due to the duration of the study and the placebo effect, which could contribute to patients abandoning the study because they consider the medication they are given is having no effect.

Follow-up visits with controls every 3 months will allow us to balance recommendations on treatment compliance and increase the possibility of detecting adverse effects. This will give us greater control over the development of the study.

As regards problems of external validity, the participants may not represent all eligible subjects if the rate of non responders were high. Furthermore, the study population characteristics (socio-economic level, life-style, etc.) may mean that the results cannot be directly transferred to any other population.

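### Effect modification is examined only after the raw and adjusted RR differ, a trigger that in a randomised trial reflects chance imbalance rather than effect modification

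*Protocol article*

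**What the plan says.** The Statistical analysis section of the protocol article sets out this sequence:

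- A baseline comparison of the arms: "We will determine if, despite using randomized assignment, the two groups are homogenous".
- A raw analysis (ARR, RRR, NNT with confidence intervals), followed by adjustment: "A stratified analysis will also be performed adjusting for each independent variable".
- A conditional step: "If there are differences between the raw RR and the adjusted RR, the homogeneity between the categories will be determined". Its stated purpose is "to establish if the variable is effect modifying or confounding".
- Kaplan-Meier, log-rank and then a Cox model for the effect of treatment on falls.

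The candidate variables are under Definitions of the primary variables and measuring methods. One group is "Stratification and potentially confounding variables; gender, age and other demographic data (social class, education level, marital status"); the other is "Risk factors for falls: taking pre-disposing medication, health problems, toxic habits, physical exercise, living arrangements, sight or hearing difficulties, functional status (Katz index"). The article describes no subgroup or interaction analysis outside the conditional step. On randomisation, the Discussion says: "Confounding is also reduced because randomization tends to share the determining factors that may affect the final result equally among the groups".

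**The concern.** Comparing a raw with an adjusted RR is a check for confounding. Effect modification is a different question: whether the RR differs between categories of a factor. The plan uses the first as a gate to the second. Randomisation balances factors on average, so the raw and adjusted RR should lie close together whether or not the effect is uniform. The Discussion's own sentence on randomisation leads to the same expectation.

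At stake is who benefits. The Background reports that existing evidence supports individualised use, especially in people deficient in calcium or vitamin D, and that earlier studies differed in baseline vitamin D status. Calcidiol is measured at baseline, with deficiency defined as below 10 ng/ml. If the gate were applied with any meaningful threshold, a real difference of this kind would usually go unexamined, and a variable could be labelled confounder or modifier because of a chance imbalance.

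**Working it through.** **Inputs from the protocol (Sample size):** falls 30% versus 20%, so RR 0.667; alpha 0.05; power 80%; 293 evaluable per arm; equal arms.

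**Assumed, because the article gives no values:** one binary factor splitting patients evenly, the stratum risks below, and gates of 1%, 5% and 10% relative difference between raw and adjusted RR.

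**1. The plan's own figure.** Two-sided, without continuity correction:

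n = [1.96·√(2·0.25·0.75) + 0.8416·√(0.3·0.7 + 0.2·0.8)]² / 0.10² = (1.200 + 0.512)² / 0.01 ≈ 293 per arm (294 rounded up).

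The stated 293 is reproduced.

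**2. Why the gap does not measure modification.** In stratum s let a and b be the falls, and t and c the patients, in the treated and control arms, with N = t + c. The Mantel-Haenszel adjusted value is

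RR_adj = Σ(a·c/N) / Σ(b·t/N).

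If the arms are balanced within strata (t = c), every weight is 1/2 and RR_adj = Σa/Σb. With equal arms that is exactly the raw RR, whatever the stratum-specific RRs are.

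- *Strong modification, perfect balance.* Control risk 30% in both halves, treated risk 30% and 10% (RR 1.0 and 0.33). Raw RR = (0.5·0.30 + 0.5·0.10)/0.30 = 0.667. Adjusted RR = 0.667. Gap: zero.
- *No modification, chance imbalance.* Control risk 20% and 40%, RR 2/3 in both strata, with 55% of treated and 45% of control patients in the high-risk stratum. Raw RR = (0.45·0.1333 + 0.55·0.2667)/(0.55·0.20 + 0.45·0.40) = 0.2067/0.29 = 0.713. Adjusted RR = 0.667. Gap: 0.667/0.713 − 1 ≈ −6%.

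The gate stays shut in the first case and opens at 5% in the second, the reverse of what is wanted.

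**3. How often this happens.** Simulation with 293 per arm, simple 1:1 randomisation and 40,000 trials per scenario. Heterogeneity is tested by z = (ln RR₁ − ln RR₀)/√V, with V = Σ(1/a − 1/t + 1/b − 1/c) over the two strata (0.5 added to each count), at p < 0.05.

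| Scenario (control risk by stratum) | Median gap | Gap > 5% | Detected, direct test | Detected behind 5% gate |
|---|---|---|---|---|
| No modification, prognostic factor (20%/40%) | 1.8% | 7.7% | 4.8% (false positive) | 0.4% |
| RR 1.0 vs 0.33 (30%/30%) | 1.3% | 2.8% | 93.2% | 2.7% |
| RR 1.0 vs 0.5 (20%/40%) | 0.8% | 0.6% | 62.4% | 0.3% |
| RR 1.33 vs 0.33 (20%/40%) | 0.2% | 0.005% | 99.6% | 0.005% |

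Behind a 10% gate, detection is at most about 0.02% in the three scenarios with modification. For RR 1.0 versus 0.33, a 1% gate gives about 57%. If any difference at all opens the gate, it opens in about 97% of trials and detection is about 90%.

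Hand check of the 93%: with 146.5 patients per cell, expected falls are 14.65 in one treated cell and 43.95 in each of the other three. V = (1/14.65 − 1/146.5) + 3·(1/43.95 − 1/146.5) = 0.109, so z = ln 3/√0.109 = 3.32 and power is Φ(3.32 − 1.96) ≈ 0.91, close to the simulated value.

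**4. Milder heterogeneity.** RR 0.5 versus 0.83 with 30% control risk: expected treated falls are 21.98 and 36.63, V = 0.091, z = 0.511/0.302 = 1.69, and power is Φ(1.69 − 1.96) ≈ 0.39.

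**5. Many adjusted results.** In null simulations with 5 and 12 covariates (4,000 trials each), type I error was 5.6% and 5.0% for the raw test. It was 5.1% and 4.6% when adjusting for the most imbalanced covariate, and 7.9% and 7.0% if the most favourable of the raw and all single-variable results were reported.

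**The case against.** **The threshold is not in the text.** The article says only that the values differ. Read literally, almost any trial passes the gate and little detection is lost (about 90% against 93%). This stands: the loss depends on a threshold that the analyst would have to choose. It does not rescue the rule, because a gate that nearly always opens does no work and one with a material threshold closes on the wrong trials.

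**The strong scenarios flatter the remedy.** This also stands. Direct testing detects about 39% at RR 0.5 versus 0.83, and 15 to 19% if the more responsive group is only 20 to 30% of patients (RR 0.5 versus about 0.75). Removing the gate does not make the trial powerful for modest interactions.

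**Modification is not an objective, and the main comparison is unaffected.** Correct. The trial is sized for the overall effect, and the raw, log-rank and Cox comparisons by intention to treat do not use the gate. Baseline calcidiol is not in the listed stratification or risk-factor groups, so naming it is a suggestion, not the correction of an error.

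**Covariates and subgroups may be specified elsewhere.** The Cox covariate list and subgroup details may sit in the full protocol or SAP, so their absence here is not criticised. The gate is different: it is a rule that the article states.

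**Adjustment chosen from imbalance.** A reader might infer that covariates are selected because the arms look unequal at baseline. The text does not say so. It adjusts for each variable, ties no adjustment rule to the baseline comparison, and names no baseline significance tests. Adjusting for the most imbalanced covariate did not inflate type I error in the check above.

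**Conclusion.** The point holds for the gate. A raw-versus-adjusted RR difference is uninformative about effect modification in this randomised design, its size is left undefined, and it is then used to label variables. At 293 per arm, with RR 0.33 versus 1.0 in equal halves, detection falls from about 93% with direct testing to about 57%, 3% and under 0.1% behind gates of 1%, 5% and 10%. A 5% gate opens more often with a prognostic factor and no modification (about 8% of trials) than with any of the strong modifiers tried (at most 2.8%). These figures rest on the assumed split, stratum risks and gates. The direction does not: it follows from the algebra in step 2.

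Two stronger readings are not supported. Randomisation does not rule out raw-adjusted differences; it makes them small on average, and the Discussion claims no more than a tendency to balance. Nor can it be said that the trial would be unable to find a modifier: the stratified analyses produce stratum-level data, nothing forbids testing them, and a literal reading of the trigger loses little. The consequence is confined to a secondary, exploratory step.

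**What to change.** 1. Delete the raw-versus-adjusted trigger and the confounder-or-modifier labelling that follows from it.
2. Name a few factors in advance, all already collected (for example sex, age, and baseline calcidiol below 10 ng/ml). Test treatment-by-factor interaction directly for each, whatever the raw-adjusted difference. Report stratum-specific effects with confidence intervals and label the analyses exploratory.
3. Present the single-variable adjusted RRs as sensitivity analyses beside the unadjusted intention-to-treat result, so that none of them can take its place after the fact.

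The cost is wording only; no new data or visits are needed. The remaining limitation is low power for modest interactions, which the text should acknowledge so that a non-significant interaction test is not read as proof of a uniform effect.

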### Study objectives

The first objective is to determine the efficacy of calcium and vitamin D supplementation at doses of 1200 mg and 800 IU, respectively, to reduce the incidence of falls and fractures in non-institutionalized elderly people.

The second objective is to measure and compare treatment groups (calcium and vitamin D vs placebo) as regards muscle strength and musculoskeletal function, bone mineral density, calcidiol level and treatment safety.

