- Treatment compliance. To determine this, the patient will bring the medication containers (empty or partially empty) to each visit. According to their degree of compliance (difference between number of tablets dispensed and number of tablets consumed) the patients will be classified as normal compliers (89-100%), hypercompliers (> 110%) or hypocompliers (< 80%). Compliance will also be evaluated by the Morisky-Green test.

- Serious adverse events or any other adverse event. An adverse event is considered as any untoward medical occurrence in any patient included in the study which does not necessarily have a causal relationship with the treatment. An adverse event can therefore be any unfavorable and unintended sign (including an abnormal laboratory finding), symptom, or disease temporally associated with the use of a medicinal product. Known adverse events of the calcium vitamin D combination at the proposed doses are: occasionally slight gastrointestinal alterations and the possibility of stimulating kidney stone formation in patients with impaired renal function.

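### The analysis of calcium and vitamin D levels conditions on post-randomisation compliance, so it does not estimate the randomised group difference

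*Protocol article*

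**What the plan says.** All references are to the protocol article.

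- **Statistical analysis, the model for levels:** "The effect of treatment on calcium and vitamin D levels will be estimated adjusted for changes in treatment compliance", using "generalized linear models for repeated measures". The model is not labelled supportive or exploratory, and no other analysis specific to these levels is named.
- **Statistical analysis, the general principle:** intention to treat, "including all randomized patients in the efficacy and safety analyses according to their randomized treatment group regardless of the treatment received". The exception is limited: "A per protocol analysis will also be performed for the primary variables". The primary variable is falls, so the exception does not reach calcium or calcidiol.
- **Definitions of the primary variables and measuring methods, compliance:** "the patient will bring the medication containers (empty or partially empty) to each visit", and the degree of compliance is the "difference between number of tablets dispensed and number of tablets consumed".
- **Same section, calcidiol:** a secondary variable, "determined by RIA at baseline and at 6 and 18 months". Serum calcium is also listed as secondary.
- **Study objectives:** "The second objective is to measure and compare treatment groups", with calcidiol level among the measures to be compared.

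**The concern.** Compliance as defined here can only be observed once tablets have been dispensed. It lies on the path from assignment to serum level, and it may share causes with that level, such as general health or diet. Holding it fixed compares patients who took similar numbers of tablets. Randomisation does not make those patients comparable.

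Calcidiol change is the measure that shows how far the supplement altered vitamin D status. A distorted group difference would affect how that exposure is reported and how the falls result is interpreted beside it.

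The article itself suggests two ways in which compliance could differ by arm. The list of known adverse events includes occasional mild gastrointestinal effects of the active combination, which could lower compliance on active treatment. The Discussion foresees patients giving up because they perceive no benefit, which could lower it on placebo. The two act in opposite directions.

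**Working it through.** **Nothing to reproduce.** The plan gives no expected calcidiol or calcium difference and no expected compliance by arm. Its evaluable sample size of 586 is set for the proportion with falls and does not enter here.

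**Timing and meaning of compliance.** Containers come back at visits after randomisation, and the measure is tablets consumed. Compliance is therefore a consequence of assignment plus patient behaviour, not a baseline covariate.

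**Formula.** Suppose compliance enters the linear model as one term common to both arms (an assumption, since the article does not give the form). Then

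adjusted coefficient = intention-to-treat difference - b x g,

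where g is mean compliance on active minus placebo and b is the pooled within-arm slope of level on compliance. The two estimates agree if g = 0 or if b = 0. They differ only when both are non-zero.

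**Assumed inputs (none from the article).**
- Compliance is 0.8 on placebo and 0.8 + g on active, plus 0.1 x U plus independent noise with SD 0.1, limited to the range 0 to 1.1. U is an unmeasured health factor with SD 1.
- Level = 20 + 2 x U + 10 x compliance (active arm only) + noise with SD 4.

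**By hand, ignoring the limits on compliance.**
- Within-arm variance of compliance: 0.1² + 0.1² = 0.02.
- Slope on placebo: (2 x 0.1)/0.02 = 10.
- Slope on active: 10 + 10 = 20.
- Pooled over equal arms: b = (10 + 20)/2 = 15.
- At g = -0.10: intention-to-treat difference 10 x 0.70 = 7.0; adjusted 7.0 + 1.5 = 8.5.
- At g = +0.10: intention-to-treat difference 10 x 0.90 = 9.0; adjusted 9.0 - 1.5 = 7.5.

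**By simulation (400,000 patients per scenario).**

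| Gap, active minus placebo (points) | Intention-to-treat difference | Compliance-adjusted | Adjusted minus ITT |
|---|---|---|---|
| -10 | 6.98 | 8.47 | +1.49 |
| -5 | 7.48 | 8.23 | +0.75 |
| 0 | 7.98 | 7.98 | 0.00 |
| +5 | 8.48 | 7.75 | -0.73 |
| +10 | 8.96 | 7.51 | -1.45 |

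Relative to the randomised difference, the extremes are 1.49/6.98 = +21% and -1.45/8.96 = -16%.

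**Dependence on the assumptions.** With no shared cause (coefficient of U on level set to 0), the slopes are 0 and 10, so b = 5 and a 10-point gap moves the estimate by 0.5 instead of 1.5. If an arm-by-compliance term is added to the simulated model, the arm coefficient refers to zero compliance. It lies between -1.40 and 1.05 over the same gaps and no longer describes the group difference at all.

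**The case against.** Several points on the other side are sound.

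- **Intention to treat.** A reader might infer that the plan contradicts its own intention-to-treat statement. That goes too far. The statement fixes who is analysed and in which group; a covariate excludes nobody and moves nobody. What remains is a tension about the effect being estimated.
- **Direction.** A reader might infer that the model will inflate the effect, or show one where there is none. The article does not support a direction, because its two routes to unequal compliance oppose each other. A spurious effect would also require that the supplement leaves calcidiol unchanged.
- **Conditions.** A difference in compliance between arms is not enough. Compliance must also be related to level within arm. That is to be expected where the tablets work, but the article gives no figure for it.
- **Likelihood of a large gap.** Identical-looking placebo, double blinding and three-monthly visits intended to even out compliance advice all make a large gap less certain.
- **Model form.** The article does not say whether compliance enters as a common term, by arm, by visit or in categories. Calling the model misspecified would criticise a form it does not state, and such detail may properly sit in a fuller document.
- **Other analyses.** The general comparison of proportions could cover vitamin D deficiency as a yes/no variable. It would not give the treatment effect on the levels themselves.

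These points limit size and certainty. They do not change the fact that the one analysis named for the levels conditions on a post-randomisation measure of treatment received.

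**Conclusion.** The point holds as a problem with the effect estimated on secondary biomarkers. The stated model does not deliver the randomised comparison of calcidiol that the second objective calls for.

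In the illustration the estimate is off by about 0.7 units for a 5-point compliance gap and about 1.5 units for a 10-point gap, on a randomised difference of roughly 7 to 9. The sign depends on which arm complies less, and there is no discrepancy when compliance is equal. These sizes rest wholly on the assumed inputs and a common compliance term. That bias is possible in either direction follows from the method.

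It should be fixed, but it does not threaten the trial's main conclusion. The raw risk measures, chi-squared test, Kaplan-Meier and log-rank analysis and Cox model for falls are untouched, as is the sample size.

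**What to change.** - **Main analysis.** For calcidiol, specify a repeated-measures model at 6 and 18 months with randomised arm, visit, arm-by-visit interaction and the baseline value as covariate, and no compliance term. Use the same structure for serum calcium at the post-baseline visits where it is measured. Report the arm difference at each visit with its confidence interval.
- **Compliance analysis.** If an effect in patients who take the tablets is of interest, label it supplementary and estimate it with a method that respects randomisation, such as a complier-average effect with randomised arm as the instrument. Also report compliance by arm.

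**Cost.** A change of wording only. Calcidiol is already planned at baseline, 6 and 18 months, laboratory tests are scheduled before treatment starts, and tablet counts are already collected. No visit, sample or patient is added.

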### Intervention

The pharmacological intervention will be the daily administration of chewable tablets containing 800 IU of vitamin D and 1200 mg of calcium. They will be administered over 2 years during the months of November to April in order to avoid the influence of sunlight. Dose adjustment is not contemplated during the study. Concomitant treatment with thiazide diuretics, digitalis drugs, anticonvulsants or barbiturates will not be permitted.

The control drug will be chewable placebo tablets with the same appearance as the test drug.

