### Subject follow-up

The subjects will be followed up for a 2 year period. They will be selected at primary care doctor visits, when they will be asked to participate in the study. Once the patients have given their informed consent they will be given an appointment for the randomization visit and an appointment for the analytical tests and densitometry examination before starting treatment.

At the randomization visit the patient will be assigned to one of the study groups, their medical history will be taken, they will be given a physical examination and the study medicine will be dispensed. The following visits will be at 3, 6, 9, 12, 15, 18, 21 and 24 months. At these visits the efficacy (data on falls, fractures, muscle strength and mobility and musculoskeletal function) and safety (the detection of adverse effects) parameters will be collected, treatment compliance will be evaluated and the medication will be dispensed.

Discontinuation of treatment will be for the following reasons: completion of follow-up period (two consecutive years), death, violation of protocol, adverse event, inter-current illness causing immobilization for more than 30 days and patient abandoning trial or withdrawing informed consent.

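### Safety is compared only by randomised arm, with no exposure-based analysis, although tablets appear to be given in only about 12 of 24 months; this mutes the signal for acute adverse effects

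*Protocol article*

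**What the plan says.** **Analysis set.** Under Statistical analysis, the protocol article states one rule for efficacy and safety together: "including all randomized patients in the efficacy and safety analyses according to their randomized treatment group regardless of the treatment received". The only other set named there is limited to the falls side: "A per protocol analysis will also be performed for the primary variables". No safety analysis by treatment received or by time on treatment is given.

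**Dosing.** Under Intervention: "They will be administered over 2 years during the months of November to April in order to avoid the influence of sunlight".

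**Follow-up and collection.** Under Subject follow-up: "The subjects will be followed up for a 2 year period" and "The following visits will be at 3, 6, 9, 12, 15, 18, 21 and 24 months". The same section says that at these visits "safety (the detection of adverse effects) parameters will be collected, treatment compliance will be evaluated and the medication will be dispensed". The adverse event definition, under Definitions of the primary variables and measuring methods, covers any untoward occurrence in an included patient and sets no explicit on-treatment limit.

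**Use of the safety data.** Treatment safety is part of the second objective. An intermediate analysis is also planned "to decide if the study should be discontinued prematurely because of frequent adverse effects occur", or for clear benefit.

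**The concern.** Keeping everyone in the assigned arm is the cautious choice for a superiority claim on efficacy, because non-exposure pulls the arms together. For harm, the same pull works in the reassuring direction. This trial has two sources of it:

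- **Planned off-drug time.** If tablets are taken only from November to April, half of follow-up is off drug even with perfect compliance. Events in those months enter both arms at the background rate.
- **Unexposed patients.** Anyone in the active arm who never starts or who stops still counts as treated. An adverse event is itself a listed reason for stopping.

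At stake is whether the trial could recognise a real excess of acute effects. The article names slight gastrointestinal disturbance as a known effect. It also foresees a recommendation for the elderly population if the supplement works, so an unremarkable safety table would carry weight.

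**Working it through.** **Inputs from the protocol article**
- Months on tablets: November to April is 6 per year, so 12 of 24 (50%).
- Adverse effects collected every 3 months to month 24.
- Patients per arm: 704 / 2 = 352 (Sample size).

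The article gives no adverse-event rates and no safety power, so there is no stated figure to reproduce. All risks below are assumptions.

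**Model.** Let b be the placebo risk and e the active risk over the 12 on-drug months. Harm acts only while on tablets, and the off-drug months carry risk b in both arms. Everyone is exposed as assigned. Over 24 months:
- placebo risk p0 = 1 − (1 − b)²
- active risk p1 = 1 − (1 − e)(1 − b)

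Power (two-sided 0.05) = Φ[(d − 1.96·SE0)/SE1], where d is the risk difference and SE0 and SE1 are the pooled and unpooled standard errors.

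**Main case, b = 10%, e = 15%**
- On-drug months: ratio 0.15/0.10 = 1.50; excess 5.0 points. SE0 = √(0.125 × 0.875 × 2/352) = 0.02493; SE1 = √((0.0900 + 0.1275)/352) = 0.02486. Power = Φ[(0.05 − 0.04886)/0.02486] = Φ(0.05) = 52%.
- All 24 months: p0 = 1 − 0.90² = 19.0%; p1 = 1 − 0.85 × 0.90 = 23.5%. Ratio 0.235/0.190 = 1.24; excess 4.5 points. SE0 = 0.03084; SE1 = 0.03079. Power = Φ[(0.045 − 0.06044)/0.03079] = Φ(−0.50) = 31%.

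**Range of assumed risks**

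| On-drug risks | 24-month risks | Ratio | Excess (points) | Power |
|---|---|---|---|---|
| 2% vs 4% | 4.0% vs 5.9% | 2.00 → 1.49 | 2.0 → 1.96 | 34% → 22% |
| 5% vs 9% | 9.8% vs 13.6% | 1.80 → 1.39 | 4.0 → 3.8 | 55% → 35% |
| 10% vs 15% | 19.0% vs 23.5% | 1.50 → 1.24 | 5.0 → 4.5 | 52% → 31% |
| 30% vs 38% | 51.0% vs 56.6% | 1.27 → 1.11 | 8.0 → 5.6 | 61% → 32% |

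Ratio and power fall in every row. The absolute excess falls materially only where events are common.

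**Cross-check with constant rates.** If the on-drug rate ratio is R and half the time is on drug, the whole-follow-up rate ratio is (R + 1)/2, so 2.0 becomes 1.5. With a background of 0.05 per year and R = 2:
- one on-drug year: 1 − e^(−0.05) = 4.9% vs 1 − e^(−0.10) = 9.5%; excess 4.6 points, power 66%
- two years: 1 − e^(−0.10) = 9.5% vs 1 − e^(−0.15) = 13.9%; excess 4.4 points, power 44%

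The pattern is the same.

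**Unexposed patients.** If a share f of the active arm takes no tablets, the excess is multiplied by (1 − f). In the main case, an assumed f of 10% takes 4.5 points to 4.05 and power from 31% to 26%. The article gives no value for f.

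**The case against.** **The quoted rule fixes who is analysed and in which arm; it fixes no event window.** This is true. The 24-month window is inferred from the visit schedule and the adverse event definition. That definition also speaks of events linked in time to use of the product, and an analysis plan not shown could set an on-treatment window. But treatment received is expressly set aside for safety, and the one exposure-related set is confined to the primary variables. That choice is stated, not left open.

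**The 50% figure relies on one side of a conflict.** This stands. Dispensing medication at every visit from month 3 to month 24 does not fit a November to April course. If dosing were continuous, the off-drug part of this point would disappear and only the part about treatment received would remain.

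**A reader might infer that the rule dilutes any real excess of harm.** The documents do not support that. For uncommon events the absolute excess is almost unchanged; what falls is the ratio and the power. Power lost to background events is imprecision, not a biased excess risk. Harms that appear late, possibly kidney stones, may surface in off-drug months, where whole-follow-up counting helps to find them.

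**A reader might also infer that the interim safety decision is biased towards continuing.** The article gives no timing, test or threshold for that look, so the share of off-drug time at that point is unknown.

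**Never-treated or crossed-over patients may be few.** Medication is handed out at the randomisation visit, and the tablets are coded and identical. This is fair, and it is why no size is claimed for that part.

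**Conclusion.** The point holds in a limited form. The one stated safety rule ignores exposure in a trial that, on its Intervention section, has planned off-drug periods. For acute effects this pulls risk ratios towards 1 and costs power: 1.50 to 1.24 and 52% to 31% in the main case, with power losses of about 12 to 29 percentage points across the assumed risks in the table. The absolute excess changes little unless events are common.

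The result rests on four assumptions: the seasonal course in the Intervention section, adverse events counted through month 24, harm confined to time on tablets, and event risks that the article does not give. It does not show that the whole safety comparison is biased towards no harm, nor that whole-follow-up counting is wrong. It shows that this counting should not stand alone. The change is worth making, but the point does not threaten the trial.

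**What to change.** 1. Keep the by-arm, whole-follow-up safety analysis; it is needed for delayed harms.
2. Add beside it, with equal standing, a safety analysis of patients who took at least one tablet, by treatment actually received. Report adverse events separately for dosing and non-dosing periods, with absolute differences as well as ratios.
3. Look at both analyses at the interim safety review.
4. Reconcile the November to April course with the dispensing of medication at every visit, so that the dosing periods used in step 2 are defined.

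The cost is a sentence in Statistical analysis and one extra table. Adverse effects and compliance are already collected every 3 months; onset dates are needed to place events in a period. The downside is a safety set that differs slightly from the randomised set, which is why the by-arm analysis stays alongside. No treatment or visit changes as a result of steps 1 to 3.
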